This study will use comprehensive nationwide data and apply machine learning (ML) methods to develop a CRC risk prediction model. PWoH will be included to increase statistical power. Matching will be used to control for key confounders, and appropriate methods will be applied to minimise bias and prevent overfitting during model development. Sensitivity and subgroup analyses will be conducted to compare model performance across different scenarios. ML-based prediction models may be superior to logistic or Cox proportional hazards (PH) regression-based models. Previous research studies have compared these approaches, resulting in varying conclusions. Some ML methods have been observed to perform as good as, or may be favourable to, Cox PH or logistic regression for some prediction tasks.^8–12^ Logistic or Cox PH regression methods may perform prediction tasks better or worse than some ML approaches,^11^ but data-driven approaches using ML have been favoured in some studies due to their ability to understand complex relationships in data, which may have an advantageous prediction performance.^12^ It may be more difficult to motivate an ML approach in a resource- or time-limited setting, in particular if data quality or dimensionality is lower and Cox PH or logistic regression methods can complete prediction tasks to a comparable level.

This protocol will use an ensemble method called stacking,^13^ which will combine the predictions of multiple ML models to produce an overall predicted risk score of CRC. Each ML method relies on different statistical assumptions and processes that may reflect different patterns in the data and offer unique insights into the relationships between variables and the outcome.^14^ By leveraging the estimates from each model in the ensemble, the perspectives from diverse model approaches can be integrated to create a more robust and accurate prediction.^15–17^ The performance of the ensemble model approach will be compared with the performance of a Cox PH regression model.

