### Study aims

The aim of this study is to apply a range of ML methods to analyse comprehensive datasets collected from nationwide demographic and health registers in Sweden to develop CRC risk prediction models for PWH, additionally using data from PWoH and compare the performance to a Cox PH regression model prediction baseline. Additionally, the aim is to evaluate the importance of variables to the prediction models.

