#### Data preparation

For this study, we will use complete cases only since missing data are minimal. Variables missing more than 10% of the data will be omitted, and after that, any observations with missing data will be dropped.^32^ For the ML analyses, the data will be split 80% into training and 20% into test sets based on follow-up time. The variables in each set will be further prepared to optimise their analysis. Categorical variables will be transformed using one-hot encoding. Normalisation and standardisation of variables will be applied where necessary.

The participants will be matched 1:10 using the entire HIV-negative population in Sweden that fit the criteria. They will be matched on age, legal sex, region of birth and comorbidities including hypertension, chronic obstructive pulmonary disease, diabetes and previous cancer diagnosis.^33
34^ The standardised mean difference of the cohorts will be compared from before and after matching to confirm consistency. Power was calculated using the full anticipated study population consisting of just over 13 000 PWH matched 1:10 to approximately 130 000 PWoH. Median follow-up time is estimated to be at least 10 years in both groups. The expected incidence rate of CRC used for the calculation was the Swedish age-standardised incidence rate reported by the European Commission (129.1 per 100 000 population).^35^ Based on these assumptions and using a two-sided alpha of 0.05, the study is estimated to have 80% power to detect an HR of approximately 1.20 or greater.

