#### Stacking and dissemination

Stacking, an ensemble learning method, will be used to combine predictions from the previously described ML models.^43^ The base learners will generate out-of-fold risk scores using Time Series Split, which will then serve as inputs to a Cox-PH model as the meta-learner. Finally, the trained base learners and meta-learner will then be used to generate final risk score predictions on the test set.

The performance of the stacked models will be primarily evaluated using balanced accuracy,^44^ and additionally assessed with the concordance index,^45^ Brier score,^46^ time-dependent area under the curve and area under the precision-recall curve (AUPRC), before variable importance is assessed.^13
47
48^ All metrics will be thoroughly considered, but the balanced accuracy of each prediction performance will be weighted most due to its handling of class imbalance, considering both sensitivity and specificity.^44^ AUPRC is preferred over area under the receiver operating curve due to its ability to better handle class imbalance, which will be a factor in this study.^49^

The model reporting will adhere to the TRIPOD+AI statement.^50^ The variable importance results will additionally be considered separately. A summary of the analysis plan is illustrated in figure 2.

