#### Substudy—PWH only

An analysis will be conducted with PWH only. A simple Cox PH regression model will be developed using preselected covariates using existing knowledge of risk factors. An exploratory approach will be followed, implementing ML methods to handle overfitting and class imbalance as needed. The prediction performance will be assessed using the same methods as the previous models and compared.

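### The main performance assessment and the choice between Cox and ensemble rest on a pooled test set, mostly people without HIV, although the model is meant for people with HIV

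*Protocol article*

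**What the plan says.** - **Target.** Under Study aims, the purpose is "to develop CRC risk prediction models for PWH, additionally using data from PWoH". The Introduction gives statistical power as the reason for including PWoH.
- **Cohort.** Under Data preparation: "Power was calculated using the full anticipated study population consisting of just over" 13 000 "PWH matched 1:10 to approximately" 130 000 PWoH.
- **Split.** In the same section, for the machine learning analyses, "the data will be split 80% into training and 20% into test sets based on follow-up time". The HIV mix of the test set is not stated.
- **Evaluation.** Under Stacking and dissemination, "the trained base learners and meta-learner will then be used to generate final risk score predictions on the test set". Balanced accuracy carries most weight among the metrics. No restriction to PWH is given.
- **Choice.** The Abstract says that whichever of Cox and ensemble performs better will be used to build the model for PWH.
- **PWH-only work.** The substudy fits a simple Cox model in PWH, with machine learning as an exploratory addition where needed. Then: "The prediction performance will be assessed using the same methods as the previous models and compared".
- **Subgroups.** The Introduction adds: "Sensitivity and subgroup analyses will be conducted to compare model performance across different scenarios". No subgroups are named.

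**The concern.** The question is which method predicts CRC better in PWH. The stated evaluation answers a different one: which method predicts better in a matched mixture with ten PWoH for each PWH. The two answers can differ. HIV-specific predictors such as CD4 count, viral load and antiretroviral treatment vary only among PWH, and a pooled score gives little weight to how well a method uses them. A method could win on the pooled set through its performance in PWoH and be carried forward for PWH while being the weaker, or the less well calibrated, of the two in that group.

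**Working it through.** **Inputs from Data preparation.** 13 000 PWH and 130 000 PWoH; 20% test set; CRC rate 129.1 per 100 000, taken as per year; follow-up: "Median follow-up time is estimated to be at least 10 years in both groups".

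**Assumptions, not in the article.** The split by follow-up time roughly keeps the 1:10 ratio. The Cox baseline is scored on the same test set as the ensemble. Mean follow-up is 10 years, with 15 as an alternative. The hazard ratio (HR) for PWH against PWoH is 1.0, 1.2 or 1.5. The same rate applies throughout.

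**The plan's own figure.** The article gives no test-set event count. Its only related figure is 80% power for an HR of about 1.20. By Schoenfeld's formula with allocation 1/11 this needs (1.960 + 0.842)² / [(1/11)(10/11)(ln 1.2)²], about 2 858 events. At exactly 10 years the inputs give 143 000 × 0.001291 × 10 = 1 846 events (1 880 at HR 1.2), power of about 62% and a detectable HR of about 1.25. About 15 years gives 1.20. The words at least and approximately leave room for this, and the figure concerns an HR test, not prediction. I use it only as a reason to show 15 years beside 10.

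**Share of people.** 130 000 / 143 000 = 90.9% PWoH. The test set would hold 0.2 × 13 000 = 2 600 PWH and 0.2 × 130 000 = 26 000 PWoH.

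**Test-set events** = number of people × 0.001291 × years (× HR for PWH).

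| Years | HR | PWH events | PWoH events | PWoH share of events |
|---|---|---|---|---|
| 10 | 1.0 | 33.6 | 335.7 | 90.9% |
| 10 | 1.2 | 40.3 | 335.7 | 89.3% |
| 10 | 1.5 | 50.3 | 335.7 | 87.0% |
| 15 | 1.0 | 50.3 | 503.5 | 90.9% |
| 15 | 1.2 | 60.4 | 503.5 | 89.3% |
| 15 | 1.5 | 75.5 | 503.5 | 87.0% |

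**If the split disturbs the ratio.** Suppose the PWH share of the test set doubled to 2/11. The PWoH share of events would be 9/11 = 82% at HR 1.0, and 9 / (9 + 2 × 1.5) = 75% at HR 1.5. PWoH would still dominate.

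**How this can turn the choice.** At a common threshold and HR 1.0, pooled balanced accuracy is about 0.909 × its value in PWoH + 0.091 × its value in PWH. Take a method 3 points better in PWoH and 20 points worse in PWH (illustrative figures). Its pooled difference is 0.909 × 3 − 0.091 × 20 = +0.9 points, so it wins. This shows that a wrong choice is possible, not how likely it is.

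**Precision in held-out PWH with 34 events and 2 566 non-events.**
- Balanced accuracy at assumed sensitivity = specificity = 0.7: SE = 0.5 × √(0.21/34 + 0.21/2 566) = 0.040; 95% half-width 1.96 × 0.040, about 0.08.
- AUC assumed 0.75, Hanley–McNeil: Q₁ = 0.75/1.25 = 0.600 and Q₂ = 2 × 0.5625/1.75 = 0.643. SE = √{[0.1875 + 33 × 0.0375 + 2 565 × 0.0804] / (34 × 2 566)} = 0.049; half-width about 0.10.
- Sensitivity alone at 0.7: 1.96 × √(0.21/n), about ±0.16 with 34 events and ±0.13 with 50, against about ±0.05 in the pooled set.

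These intervals are for one model. They do not describe the paired difference between two models scored on the same people.

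**The case against.** The strongest reply is that the article does plan work in PWH. The substudy fits Cox and, where needed, machine learning models in PWH and assesses them with the same metrics, and the Introduction announces subgroup comparisons. All metrics are to be weighed, not balanced accuracy alone. The Abstract selects a method with which to develop a PWH model, which need not mean using the pooled fit unchanged. External validation is required before clinical use. The pipeline figure is not available here.

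Much of this stands, and it rules out two stronger readings. A reader might infer that the study cannot say which model is better in PWH; the substudy means that it will say something. A reader might also infer that the substudy sets PWH-only results against pooled results and so compares populations rather than models. The text does not say this: the comparison may be between Cox and machine learning within PWH, and the scoring population for the earlier models is left open.

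The reply does not remove the gap. The substudy develops separate models, does not name the stacked ensemble, does not say that the pooled models are re-scored in PWH, and is not linked to the selection rule. The subgroups are unnamed. External validation comes after the method has been chosen.

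It is also fair to object that a choice made in held-out PWH alone would be noisy. That is correct, and it is a cost of the fix.

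**Conclusion.** The concern holds in a limited form. As written, the main assessment and the Cox-versus-ensemble choice are made on a pooled test set with no restriction to PWH, and the PWH-only substudy repairs this only in part. With a split that roughly preserves 1:10, about 91% of the test set and 87–91% of its CRC events would be PWoH. PWH would supply about 34–50 events at 10 years, or about 50–76 at 15 years, for HR 1.0–1.5. The 91% is exact for the round matched-cohort figures; for the test set it is an inference, because the split is by follow-up time. Pooled balanced accuracy would mainly reflect PWoH and could favour a method that is not the better one in PWH. The documents do not show that this will happen, or how often. The change should be made, since it goes to the study's own question and needs little extra work.

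**What to change.** Keep the planned time-based split and Time Series Split cross-validation, and state the following.

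1. Discrimination, calibration and balanced accuracy are computed for the pooled Cox model, the pooled ensemble and the PWH-only model on the same held-out PWH. The PWH-only model must therefore be trained without those people.
2. The choice of method for PWH rests primarily on these results, with a paired interval for the difference between methods.
3. Pooled and PWoH results are reported as secondary.
4. The numbers of PWH and of PWH events in the test set are reported, since the split does not guarantee them.

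The cost is a few sentences, a little computing and wider intervals. With 34 events these are about ±0.08 for balanced accuracy and ±0.10 for AUC per model, under the assumed performance levels. The article should say so, and should allow for the possibility that the data do not separate the methods in PWH. Repeated K-fold resampling over all PWH would use more events, but it would give up the time-ordered validation that the plan has chosen, so it is not part of this recommendation.

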## Abstract

**Abstract:**

**Introduction:**

There are currently no colorectal cancer (CRC) screening recommendations specifically outlined for people with HIV (PWH). Screening measures used for people without HIV (PWoH) have been previously discussed as sufficient for use among PWH, despite observations of higher CRC prevalence and CRC reportedly appearing at earlier ages among PWH in comparison to PWoH. Machine learning (ML) methods are regarded as robust approaches that may enhance predictive performance, particularly in the context of complex or high-dimensional data. This study aims to develop an ensemble ML model to predict CRC risk in PWH using comprehensive nationwide datasets. The model’s predictive performance will be evaluated and compared with a baseline Cox proportional regression model. The better-performing method will be implemented to develop a CRC risk prediction model with the aim of personalising screening recommendations for PWH.

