#### ML ensemble model—supervised ML

Elastic Net regularisation, XGBoost, Random Survival Forests and decision trees will be used to develop the ensemble model for predicting CRC risk. For Elastic Net regularisation, a Cox PH model with an Elastic Net penalty will be used to estimate relative risk and interpret variable importance via the penalised regression coefficients. The resulting model additionally highlights influential predictors by minimising less important coefficients towards zero, indicating lower contribution to predicting the outcome.^40^

Decision trees are tree-based models that split data based on variable thresholds to make predictions. Decision trees suited for survival time-to-event data will be used. This method will estimate the probability of cancer over time. This model may additionally be used to infer how much each variable contributes to reducing dataset impurity at each split,^41^ contributing to our understanding of which variables are most valuable to the outcome prediction. Random Survival Forest models work similarly to decision trees but aggregate results across many trees, providing more robust estimates of variable importance and potentially improved performance for risk prediction. XGBoost uses built-in optimisation techniques to develop high-performing prediction models.^42^ The output of the XGBoost model may additionally be used to assess the predictive value of individual variables.

Out-of-fold predictions from each model will be stored to serve as inputs for the meta-learner. Additionally, SHapley Additive exPlanations (SHAP) values will be computed for each trained base learner to assess variable contributions and enhance model transparency.

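### Balanced accuracy leads the Cox-versus-ensemble comparison, though it needs a cut-off, does not measure calibration and can favour the model with worse absolute risks

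*Protocol article*

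**What the plan says.** Under Stacking and dissemination, the base learners' out-of-fold risk scores are combined, "which will then serve as inputs to a Cox-PH model as the meta-learner", and the fitted models are then "used to generate final risk score predictions on the test set". The comparator (Cox PH regression section) is also a Cox model, so both sides produce a continuous risk.

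The same section fixes the order of the metrics: "The performance of the stacked models will be primarily evaluated using balanced accuracy". The additional measures are the concordance index, "Brier score,^46^ time-dependent area under the curve and area under the precision-recall curve (AUPRC), before variable importance is assessed". It then says "All metrics will be thoroughly considered", but adds that "the balanced accuracy of each prediction performance will be weighted most due to its handling of class imbalance".

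A decision hangs on the result. The abstract states: "The better-performing method will be implemented to develop a CRC risk prediction model". The PWH-only substudy uses the same assessment methods. The Study population section ends follow-up at emigration, death, end of study or shortly before CRC, so the outcome is censored. The Clinical relevance section intends the model to guide earlier screening, shorter intervals or referral for colonoscopy.

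**The concern.** Balanced accuracy is the mean of sensitivity and specificity. It is defined only after a risk cut-off and a horizon are chosen, and people who leave before the horizon have no observed status. It responds to calibration only by accident, as two cases show:

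- **The same absolute cut-off for both models.** The metric rewards whichever model puts its flagged group nearer the prevalence. Above the prevalence, that means rewarding overstated risk.
- **A cut-off tuned separately for each model.** Any monotone distortion of the risks then leaves balanced accuracy unchanged.

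Neither case answers the question that risk-stratified screening asks, which is whether the stated absolute risks are right.

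Class imbalance does not require this metric. Imbalance is a weakness of raw accuracy. The concordance index and the time-dependent AUC do not depend on a cut-off, and both are already in the plan.

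At stake is which method is taken forward, and whether its absolute risks are fit for screening decisions.

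**Working it through.** The plan gives no performance figure to reproduce, so this is an illustration at the plan's own event rate.

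**Inputs.** CRC rate 129.1 per 100 000 (Data preparation), taken as per year. Horizon 10 years, matching the plan's median follow-up of at least 10 years. Assumed: person-specific hazard h(x) = 0.001291 × exp(σx − σ²/2), with x standard normal and σ = 1.

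**Risk.** With a common hazard, 1 − exp(−0.001291 × 10) = 1.28%. Averaged over x with σ = 1 it is 1.27%, and the AUC is 0.76.

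**Balanced accuracy.** True risk is p(x) = 1 − exp(−10·h(x)), and predicted risk is q(x) = 1 − exp(−10·f·h(x)). Here f = 1 is the calibrated model and f = 1.5 overstates every hazard 1.5-fold. A person is flagged when q exceeds the cut-off. Sensitivity is E[p·flag]/E[p], specificity is 1 − E[(1−p)·flag]/E[1−p], and balanced accuracy is their mean. By numerical integration over x:

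| Cut-off | Calibrated (f = 1) | Overstated (f = 1.5) |
|---|---|---|
| 50% | 0.500 | 0.500 |
| 5% | 0.578 | 0.622 |
| 3% | 0.635 | 0.674 |
| 2% | 0.674 | 0.692 |
| 1.29% | 0.692 | 0.679 |
| 0.5% | 0.628 | 0.583 |

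The two columns have identical ROC curves. The calibrated model's score moves from 0.50 to 0.69 with the cut-off alone; near its maximum (cut-off 1.29%) it flags 31% of people. The overstated copy wins at 2% to 5% and loses at 1.29% and below. With the cut-off tuned for each model, both reach 0.692.

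**What the calibration-sensitive measures show.** Mean predicted risk is 1.27% for f = 1 and 1.89% for f = 1.5, against a true 1.27%. The Brier score E[p(1−q)² + (1−p)q²] is 0.01228 for the calibrated model and 0.01237 for the overstated one. The order is right, but the gap is small because the event is rare. That is why a calibration plot and slope are needed beside it.

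**Models that differ in discrimination.** Three calibrated models with σ = 0.7, 0.85 and 1.0 (AUC 0.69, 0.73, 0.76) score:

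- 0.521, 0.547, 0.578 at a cut-off of 5%
- 0.612, 0.644, 0.674 at 2%
- 0.557, 0.593, 0.628 at 0.5%

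That is AUC order each time. If the σ = 0.85 model also overstates hazards 1.5-fold, it beats the calibrated σ = 1 model at 5% (0.588 against 0.578) and 3% (0.644 against 0.635), and loses at 2% (0.665 against 0.674). A model worse on both discrimination and calibration can therefore lead on this metric.

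**Censoring.** This was simulated with σ = 0.95 and the top 30% flagged; true 10-year balanced accuracy is 0.683. Censoring unrelated to risk leaves it at 0.683 to 0.684. Censoring that rises with risk (assumed median 10·exp(−0.5x) years) gives 0.644 if censored people count as non-cases and 0.704 if they are dropped.

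**The case against.** Several points on the other side are sound.

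- **Balanced accuracy is not the sole arbiter.** The plan says all metrics will be considered, and the Brier score responds to calibration. A reader might infer that the selection is blind to wrong absolute risks. The text does not support that. It supports only that the metric given most weight is insensitive to calibration.
- **The cut-off is unstated here, not shown to be arbitrary.** A journal article may leave the cut-off and horizon to a fuller plan, so their absence is no finding. The 50% row above is a reference point; nothing in the article implies that cut-off.
- **A reader might infer that the choice between Cox and ensemble simply hangs on the cut-off.** Varying the cut-off for one model does not show that. Calibrated models kept their AUC order at the cut-offs tested from 0.5% to 5%. A reversal needs miscalibration or crossing ROC curves, and the article gives no reason to expect a particular degree of either.
- **Ignoring censoring is not inherent to the metric.** Sensitivity and specificity at a horizon can be estimated with censoring weights, and the article does not say how they will be computed. The bias shown needs risk-related censoring and naive handling.
- **Deployment is guarded.** Clinical relevance requires external validation and prospective evaluation first, which softens the consequence.
- **Competing death is a separate estimation question.** The article says of the survival trees "This method will estimate the probability of cancer over time" and ends follow-up at death, but does not say how death enters the estimate. A reader might infer a known overstatement of CRC risk. Its size depends on mortality, for which the article gives no figure.

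What remains is the stated ranking of metrics, which even a pre-specified cut-off would not repair.

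**Conclusion.** The concern holds as a point about the order of metrics. The plan puts first a threshold measure that does not assess calibration, for a rare, censored outcome with continuous predictions, and justifies this by an imbalance problem that cut-off-free measures already listed do not have. At a 10-year risk of about 1.3%, a 1.5-fold overstatement of hazards is enough for the lead metric to prefer the worse-calibrated of two otherwise identical models at cut-offs of 2% to 5%, by 0.02 to 0.04. These sizes rest on the rate being annual, log-risk SD 1, a 10-year horizon and one common cut-off. They show what can happen, not what will happen in these data. This should be changed before the comparison is run; it does not invalidate the study.

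**What to change.** In Stacking and dissemination, make the censoring-weighted time-dependent AUC and the Brier score, at one pre-stated horizon, the primary measures for comparing Cox with the ensemble. Add a calibration plot and calibration slope at that horizon. Keep balanced accuracy as a secondary, descriptive measure at a pre-stated cut-off, computed with censoring weights.

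As a secondary suggestion, where absolute CRC risk is reported, estimate it by cumulative incidence with death as a competing event.

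The cost is small. The AUC and Brier score are already planned, no new data are needed, and standard software covers the rest. The one downside is less direct comparability with earlier work that led with balanced accuracy.
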